## **7.5 Subject Withdrawal**

### **7.5.1 Reasons for withdrawal**

Participants are free to withdraw from the study at any time upon their request or the request of their legally acceptable representative.

The Research Team may withdraw a participant from the study (parent intervention and follow up procedures) if:

- During the course of the study, one of the exclusion criteria is met (e.g., the ill/injured child dies)
- The participant experiences a serious or intolerable adverse event
- Early discontinuation is required for any reason

The Researchers will also withdraw all participants from the study if the study is terminated.

### **7.5.2 Handling of withdrawals and losses to follow-up**

When a participant withdraws from the study, the participant will be contacted by a RT member to discuss their reason/s for withdrawal if they have not already informed the research team. The interviewer will open conversation regarding withdrawal or non-participating by generally asking participants about their reasons for research discontinuation. Participants can choose not to take part in the call. Once a participant has withdrawn they are not required to complete any follow-up assessments and participation in the study is discontinued. Any information gathered during the course of the study from withdrawn participants will be kept unless participants request that their information be destroyed.

If RT members are concerned about the wellbeing (e.g., elevated scores on psychometric measures) of withdrawn participants actions to ensure the safety and wellbeing of these participants will be taken (e.g., referral information will be provided, families encouraged to link in with their nurse coordinator or social worker).

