#### *Valuing Questionnaire (VQ; Smout, Davies, Burns, & Christie, 2011).*

The VQ8 is an 8-item questionnaire assessing the degree to which people live by their values and is broken down into two subscales – Progress (extent to which people felt that they lived their values in the past week) and Obstructed (the extent to which cognitive and emotional barriers interfered with acting out their values in the past week). Respondents answer items on 6 point likert scale from 0 – *not true at all* to 6 – *completely true*. The VQ8 has very good internal consistency for both factors – Progress  $\alpha = 0.90$  and Obstructed  $\alpha = 0.83$

*Acceptance and Action Questionnaire – II (Bond et al., in press).*

The AAQ-II, containing 7 items, assesses psychological flexibility/inflexibility (e.g., acceptance and experiential avoidance) on a 7 point likert scale ranging from 1 (never true) to 7 (always true). Higher scores reflect greater experiential avoidance and immobility and lower scores are indicative of greater action and acceptance. Psychometric testing reported mean alpha coefficient across the six samples tested of .84 (ranging between .78 - .88), and the 3- and 12-month test-retest reliability is .81 and .79, respectively (Bond et al., in press). Findings from these studies indicate that the measure is related to variables to which it is theoretically tied to. For example, higher levels of psychological inflexibility, as measured by the AAQ-II, are associated with greater levels of anxiety, stress, depression as well as overall psychological distress.

*Life Events Questions*

The life events questionnaire was developed by the senior investigators to obtain information about potential psychosocial stressors that participating parents may have experienced in the past 12 months (in addition to their child's serious illness/injury). The questionnaire contains a total of 14 items and asks about job loss and reduced work hours, recent pregnancies, moving home, suffering a serious illness/injury themselves, separation/divorce, or whether they have experienced an event they found traumatic. The parent is also asked to report on their partner. In addition to these items, a final 15th item was included to ask about a history of mental illness in the year prior to their child's illness/injury.

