### **11.2 Population to be analysed**

Data will be cleaned in the Statistical Package for the Social Sciences (SPSS) using procedures outlined in Tabachnick and Fidell (2007). Missing value analyses will be conducted and expectation maximisation techniques will be used to impute subscale data missing completely at random. Data will be imputed for participants completing at least 70% of items on that subscale; all other items on the subscale will be used to estimate missing data. If participants completed less than 70% of a subscale their data will be not imputed and the participant will not be included in analysis involving that subscale.

Both completer and intention-to-treat analyses will be conducted. Average closest match techniques (Elliot & Hawthorne, 2005) will be used to replace missing post and follow-up data for those who did not return questionnaires. This involves using the average post/follow-up-intervention value obtained by participants reporting the same pre-intervention score (or the four participants reporting the closest pre-intervention score), to replace the missing data for that case. This technique is considered a reliable and efficacious approach for managing missing data (Elliot & Hawthorne, 2005).

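### The withdrawal rules end data collection along with the program, so T4 is lost for withdrawn parents and the intention-to-treat analysis must impute or omit them

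*Protocol*

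**What the plan says.** Protocol section 7.5.1 opens its rule with "The Research Team may withdraw a participant from the study (parent intervention and follow up procedures) if" and lists three conditions: "During the course of the study, one of the exclusion criteria is met", with the child's death as the example; "The participant experiences a serious or intolerable adverse event"; and "Early discontinuation is required for any reason". A parent withdrawn by the team thus leaves the program and the assessments together.

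Section 7.5.2 adds: "Once a participant has withdrawn they are not required to complete any follow-up assessments and participation in the study is discontinued". Data already gathered are kept unless the parent asks for their destruction. Nothing provides for T4 from a parent who has been withdrawn.

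Section 11.2 states "Both completer and intention-to-treat analyses will be conducted". It replaces a missing post score by the average post score of participants with the same pre-intervention score, or of the four closest. It does not say whether these donors come from the same arm.

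Section 8.3 compares the arms at T2 and T4 only, and Table 2 reserves T5 for intervention families. Under the RCT Recruitment heading, allocation (items d and e) comes before the T2 questionnaires are distributed (item f).

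**The concern.** An intention-to-treat comparison needs the outcome of every randomised parent as far as it can be had. Here the protocol gives up the outcome at the moment a parent is withdrawn, including when the team and not the parent makes that decision. An analysis plan written later cannot recover a T4 that was never requested.

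The listed reasons are not neutral. A child's death or a serious adverse event is plausibly related to parental distress, which is what the PCL-5 measures. The arms are also observed differently before T4. Under section 8.2 the practitioner running the group monitors the parents attending it. That practitioner necessarily knows these are TAB parents, and wait-list parents have no group until after T4. The recruiting research assistant is told the allocation too (section 7.4). Withdrawal could therefore differ between arms and depend on how the parent is doing. Matching on the pre score alone ignores why a parent left.

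**Working it through.** **1. The route from clause to missing outcome.** Team withdrawal covers intervention and follow-up (7.5.1); participation then ends with no assessment required (7.5.2); T4 is the only post-baseline comparison between arms (8.3, Table 2). Two outcomes follow:

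- If the parent has a T2 score, T4 is imputed from parents who stayed (11.2).
- If the parent leaves between allocation and T2, there is no pre score to match on. The stated rule cannot impute a value, and the parent drops out of the analysis.

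**2. The plan's own figures (Sample Size Estimation).** Inputs: difference 6.0, SD 13.9, alpha 0.05 (taken as two-sided), power 0.80.

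- n per arm = 2 × [13.9 × (1.960 + 0.8416) / 6.0]² = 84.2, so 85. The plan states 82, at which power is 0.789. The gap is small and this point does not depend on it.
- Attrition: 2 × 82 = 164; 184 − 164 = 20; 20/184 = 10.9%. A 10% allowance reproduces the total: 82/0.90 = 91.1, so 92 per arm and 184 overall.

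The 10.9% is the allowance for all attrition, including questionnaires simply not returned. The protocol gives no rate for withdrawal under 7.5.1.

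**3. Illustrative shift in one arm's mean.** Shift = w × δ, where w is the share of that arm lost this way and δ is the gap between true and imputed T4. Both are assumed: w from 10.9% to 20%, δ from 5 to 7 points (5/13.9 = 0.36 SD; 7/13.9 = 0.50 SD).

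| w | δ | Shift (points) | Share of 6.0 |
|---|---|---|---|
| 10.9% | 5 | 0.5 | 9% |
| 10.9% | 7 | 0.8 | 13% |
| 20% | 5 | 1.0 | 17% |
| 20% | 7 | 1.4 | 23% |

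**4. Direction depends on the donors.** The closest-match rule was simulated with 92 per arm, SD 13.9, an assumed pre–post correlation of 0.5, the same loss rate in both arms, loss unrelated to the pre score, and 4000 runs. The effect in parents who benefit is 6 points. If TAB withdrawers gain nothing, the true difference over all randomised parents is 6 × (1 − w).

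| w | TAB withdrawers | True difference | Estimate, same-arm donors | Estimate, donors from both arms |
|---|---|---|---|---|
| 10.9% | gain nothing | 5.35 | 6.02 | 5.30 |
| 10.9% | benefit fully | 6.0 | 6.07 | 5.31 |
| 20% | gain nothing | 4.8 | 6.04 | 4.78 |
| 20% | benefit fully | 6.0 | 5.98 | 4.78 |

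With same-arm donors the estimate stays near 6 even when withdrawers gain nothing, so the effect is overstated. With donors from both arms it falls to about 5.3 or 4.8 even when they benefited, so it is understated. Under each donor rule the estimate is nearly the same whether or not withdrawers benefited. Only an observed T4 can tell the two cases apart.

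**The case against.** The strongest reply is that 7.5.2 concerns parents who leave the study. No section says that a parent who stops attending sessions is withdrawn. Section 8.3 collects data from all participating parents, and section 11.3 plans an analysis of compliance. This stands. A reader might infer that every TAB parent who stops sessions loses T4, but the text does not support that. How often the problem arises depends on how the team applies the word, which the protocol leaves open.

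Second, not being required to complete an assessment is not a ban on asking, and ending data collection respects a parent who chooses to leave. Both are fair. A parent who refuses further contact is outside the remedy. For a parent withdrawn by the team, however, participation is discontinued and no T4 contact is planned, so T4 will in practice be missing.

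Third, section 11.2 already promises intention-to-treat. That fixes who is counted, not whether their outcome is observed.

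Two further readings should be set aside. A reader might infer that the Life Events Questions, which ask about "a history of mental illness in the year prior to" the child's illness and about traumatic events, would trigger exclusions after randomisation. Section 6.1 applies the corresponding exclusions at screening, the form is given no eligibility role, and both arms complete it on a matched schedule. A reader might also take the protocol to exempt bereaved families from follow-up. It names the child's death only as an example of a reason for withdrawal.

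**Conclusion.** The point holds for withdrawal from the study as 7.5.1 and 7.5.2 define it, above all for withdrawal by the team. Followed as written, these sections give up the primary outcome at its only between-arm time point, for reasons plausibly tied to distress. The intention-to-treat analysis then rests on borrowed values for these parents, or omits those who leave before T2.

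Bias is possible but neither its presence nor its direction is established. The shift of 0.5 to 1.4 points (9% to 23% of the 6-point target) is an illustration. It assumes that 11% to 20% of one arm is lost this way and a gap of 5 to 7 points. Its lower rate charges the plan's whole attrition allowance to this clause, so the effect would be smaller if few parents are withdrawn. A reader might take these figures as an expected bias, but the protocol gives no withdrawal rate and no split by arm. The change is worth making because it is cheap and the data cannot be recovered afterwards.

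**What to change.** In sections 7.5.1 and 7.5.2:

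- Define stopping the program separately from withdrawing consent to data collection.
- Confine withdrawal by the team to the intervention. The grounds for stopping the program need not change.
- Request T4, at least the PCL-5, from every randomised parent who has not refused further contact, leaving the sponsor free not to approach bereaved families.
- State that all parents are analysed as randomised.

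The cost is protocol wording and one questionnaire request for a small number of parents. The downside is a small added burden on those parents; their right to refuse is unchanged. Some T4 values will still be missing, and for those the donor arm in section 11.2 should be stated. The sample size does not change.

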## **7.6 Trial Closure**

Once the designated number of participants in the study has been reached (e.g., 184 participants have been randomised the RT will inform The RCH departmental staff who have been promoting the study, that the study is closed to new participants. If potential participants contact the RT to participate, they will be provided with appropriate alternative referral options if needed. As outlined in the PDCF, participants will be provided with a summary of group outcomes of the study. It is not anticipated that the study will cease prematurely. The only foreseeable circumstance would be if funding for the study was withdrawn. However in this case the RT would seek additional funding to complete the study. Should any difficulties arise with recruiting the required number of participants, an extension to continue the study will be sought. Again additional funding will be sought to extend the study to ensure that the adequate number of participants has been achieved to complete the study.

## **8. STUDY IMPLEMENTATION SCHEDULE**

### **8.1 Screening**

A maximum of 788 parents will participate in the screening process allowing for an uptake rate of seventy per cent of these eligible parents (n = 552). Parents will be provided with the Screening Questionnaire within four weeks of their child's diagnosis.

### **8.2 Parent Intervention Groups**

A total of 263 parents will participate in the main RCT study. It is anticipated that up to 30 parent groups will be delivered. A maximum of 10 parents will be enrolled into each group to ensure that parents can participate fully in all aspects of the program.

Parent groups will be scheduled on different days and times, with evenings and/or weekends being available. Sessions will be held once per week for a total of five consecutive weeks with a sixth session held two to four weeks later. The sixth session is included as it provides parents with a short period to practice and implement the skills and ideas taught during the program and to address any difficulties or barriers that arise when implementing them. All sessions will be delivered via online videoconferencing using Google Hangouts.

Parent programs will be commenced when enough parents have been randomised to the TAB treatment arm to constitute a group (a minimum of 5). Parents randomised to the Wait List arm will receive their pre questionnaires at the same time as the parents scheduled to commence that TAB group. In this way the timing for their assessment points will be matched to the participants in the TAB treatment arm.

Parents will be monitored by the practitioner facilitating the group they are attending throughout the intervention and at each assessment point. Evaluation questionnaires will be used to support the clinical judgment of the practitioner.

### **8.3 Evaluation**

Assessment data will be collected from all participating parents. Additionally, data regarding the child's diagnosis and treatment will be extracted from the child's medical file.

#### ***Parents***

Parents will be asked to complete a series of participant measures on two separate occasions. The participant measures from the TAB arm will then be compared to the participant measures from the W-L at two time points (See Table 2 for detail).

- T2: Two weeks prior to parents attending the parent program (Pre)
- T4: Immediately following completion of the parent program (Post)

Immediately after T4 it is anticipated that parents in the W-L arm who wish to participate will have had the opportunity to register and/or participate in the TAB parent group.

It is anticipated that completion of the questionnaire package will take parents approximately twenty to thirty minutes at each data collection time point. Parents will be provided with the questionnaire and an envelope for sealing and returning the completed questionnaire to the research team. Parents will also be provided with the option of completing the questionnaires online.

505  
506  
507  
508

|                   |                                     | Parent    |                                                                                                                                                                                               |
|-------------------|-------------------------------------|------------------|-----------------------------------------------------------------------------------------------------------------------------------------------------------------------------------------------|
|                   |                                     | Week             | Task/Assessment Category                                                                                                                                                               |
| Time Point | T1: Screening         | 1  | Demographic questions
Acute Stress Disorder Scale (not for the developmental disability pilot study)                                                                                       |
|                   | T2: Pre-Assessment    | 20 | Parent posttraumatic stress
Experience of illness
Child wellbeing
Child Psychopathology
Parent wellbeing
Parent Psychopathology
General Family Functioning                  |
|                   | T3: Intervention      | 23 | Parent Program – Session 1                                                                                                                                                                    |
|                   |                                     | 24 | Parent Program – Session 2                                                                                                                                                                    |
|                   |                                     | 25 | Parent Program – Session 3                                                                                                                                                                    |
|                   |                                     | 26 | Parent Program – Session 4                                                                                                                                                                    |
|                   |                                     | 30 | Parent Program – Session 5
Parent Program – Session 6                                                                                                                                      |
|                   | T4: Post Intervention | 30 | Parent posttraumatic stress
Experience of illness
Child wellbeing
Child Psychopathology
Parent wellbeing
Parent Psychopathology
General Family Functioning
Acceptability |
|                   | T5: 6-month Follow-up | 58 | Same as pre-assessment measures only for intervention families                                                                                                                                |

509 Table 2. Implementation Schedule

510 **Screening Questionnaire**

511 *Acute Stress Disorder Scale (ASDS; R. A. Bryant, Moulds, & Guthrie, 2000)*

512 The ASDS is a 19-item self-report measure designed to assess acute stress disorders in  
513 individuals in the acute period (up to 4 weeks) following a traumatic event and who may  
514 be at risk of developing PTSD. The ASDS indexes acute stress disorder based upon the  
515 criteria of the Diagnostic and Statistical Manual of Mental Disorders 4th ed. (DSM- IV).  
516 The ASDS measures 4 cluster of symptoms - dissociation (5 items), re-experiencing (4  
517 items), avoidance (4 items) and arousal (6 items). Responses are measured on a 4-point  
518 scale ranging from Not at All to Very Much. Internal consistency for the total scale was  
519 reported to be .96 and .84 for dissociation, .87 for experiencing, .92 for avoidance and  
520 .93 for arousal.

521 *Demographic Questions*

522 A series of questions have been developed to obtain relevant demographic information  
523 from participating parents. These were developed in consultation with the chief  
524 investigators on the team, drawing on their research and clinical experience. A total of

19 items are to be completed by parents at Phase One Screening only and ask about marital status, employment status, and education completed, language(s) spoken at home.

## **Pre-Assessment Parent Intervention Group Questionnaire**

### **Primary Outcome Measure – Posttraumatic stress**

*Posttraumatic Stress Disorder Checklist – Version 5 (PCL5; Blevins et al., 2015)*

The PCL5 is a 20 item self-report instrument used to measure posttraumatic stress symptoms in parents. The 20 items assess the 20 DSM-V PTSD criteria. Parents were asked to complete the measure in relation to their child's diagnosis. The Total Score (range = 0-80) was used, with higher scores indicating greater PTSS. Internal consistency for the Total Score in the current study was  $\alpha=0.93$ .

### **Secondary Outcomes**

#### **Experience of Illness**

*Family Management Measure (FaMM; Knafl et al., 2009): measure taken from <http://nursing.unc.edu/research/famm/>*

The 45 item (53 if participant has a partner) FaMM was developed to measure how families manage caring for a child with a chronic condition/illness and the extent to which they incorporate condition management into everyday family life. There are five summated scales for all parents measuring the dimensions of Child's Daily Life, Condition Management Ability, Condition Management Effort, Family Life Difficulty, and View of Condition Impact as well as a sixth scale only for partnered parents measuring the dimension of Parental Mutuality. Due to overlap with other questionnaires in the protocol, the Parent Mutuality and Condition Management Ability are only included. Items are scored from 1 to 5, meaning strongly disagree to strongly agree. Higher scores on two of the scales (Condition Management Ability, and Parental Mutuality) indicate greater ease in managing the child's condition. Higher scores on the other two scales (Condition Management Effort, and Family Life Difficulty) indicate greater difficulty in managing the condition. Internal consistency reliability (ICR) for the scales, adjusted for inter-parental correlation, ranged from .72 to .90 for mothers and .73 to .91 for fathers (Knafl, G., et al., unpublished manuscript). Test-retest reliability was based on responses from 65 parents retested within 2-4 weeks and adjusted for inter-parental correlation. It ranged from .71 to .94.

*Parent Experience of Child Illness (PECI; Bonner et al., 2006)*

The Peci is a 25 item measure of parent adjustment to a child's serious or chronic illness. Four factors found: Guilt and Worry, Emotional Resources, Unresolved Sorrow and Anger, and Long-term Uncertainty. Bonner and colleagues (2008) (Bonner, Hardy, Willard, Hutchinson, & Guill, 2008) reported test-retest reliability correlation coefficients of .83 to .86. Internal reliability alphas were between .74 and .85. They also found adequate discriminant and convergent validity. They also found the Peci to demonstrate sensitivity to differences in participant's medical status. These results

were found in a population of paediatric cancer patients. Further testing across other medical groups would need to be conducted.

